### Data Collection and Management

#### Plans for Assessment and Collection of Outcomes

All the data is collected via e-CRFs and surveys through Research Electronic Data Capture (REDCap; Vanderbilt University), which is a secure web-based data collection platform for building and managing web-based databases and surveys [46].

#### Collection of Baseline Characteristics of GPs

The baseline characteristics of the participating GPs are collected through email correspondence and registered in REDCap by the principal investigator. The following information will be obtained: age, sex, region of Spain, type of primary health clinic, seniority as a GP, experience with randomized clinical trials, experience with research on RTIs, comfort with stopping antibiotic courses, and baseline antibiotic prescribing.

#### Collection of the Participant Data

We will collect health and personal data from the patients included in the study via REDCap, where the researchers will register basal data and evolution of the illness, and via a patient diary completed by the patients themselves. Regarding the patient’s diary, we will also create a web-based symptoms diary to make it available for all patients recruited. All patients will be able to choose between the web-based and paper version of the symptom diary. Patients will be informed about the type of data that will be collected and about their rights when being informed about the study, and will sign a consent form consenting to the use of their data. No data will be collected before the patient signs the consent form. As soon as the patient has signed the consent form, they will be given a study code and will be identified by the study code in all the study materials. The relationship between his identity and the study code will be kept in the health care center and will only be available to those who need it to fulfill their duties. Data collected in this pragmatic study is considered codified data. IDIAPJGol has license to use REDCap and the data is collected and held in IDIAPJGol servers, which comply with the European and national requirements. Data controller will be the institution (IDIAPJGol) for the study-related data and the health care institution for the health data collected to manage the patient in clinical practice. There will not be any transfer of data. Only the investigator team will have access to study datasets, and always with codified information to preserve the confidentiality of the participants involved. All the recruiting investigators will have access to REDCap platform to collect the data, each of them with their own specific credentials, and they will only have access to the patients recruited in their own setting. We will follow the FAIR (Findable, Accessible, Interoperable, and Reusable) principles: all datasets and publications will be identifiable by using a “Digital Object Identifier (DOI)” and we will share the data (as far as possible) in the Zenodo platform. We will publish the results in Open Access journals, and wherever possible, the data will be shared without delay following the Creative Commons License with Attribution (CC-BY) or the “No Rights Reserved” (CC0). Data will be saved and shared using standardized formats (txt, csv, and pdf).

### Ethical Considerations

The protocol has been approved by the Spanish Agency of Drugs and Health Products and Hospital de Sant Pau Independent Ethics Committee, Barcelona (reference number 25/233). We will follow the legislation on data protection (EU 2016/679) and its national implementation (LOPD 3/2018 of 5 Dec on the protection of personal data and guarantee of digital rights).

### Plans to Promote Participant Retention and Complete Follow-Up

The loss of follow-up data obtained from medical records and shared medication records is expected to be minimal. Outcome data from medical records be collected for all participants, except those who are discontinued by the GP or who have withdrawn informed consent before day 28. We expect some participants to be lost to follow-up in the RTI symptom diary, as we anticipate that some participants will fail to complete the electronic diary or will fail to submit the paper version to the GP. For those who do not return the diaries, participants will be contacted by phone on day 14 to gather information on antibiotic use, adherence, and symptom duration details.

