### Interventions

Patients assigned to usual care will be given a full course of the first-line antibiotic course as recommended by the updated local guidelines [34,35]: amoxicillin 750 mg 3 times daily (t.i.d.) for 7 days for acute rhinosinusitis, 1000 mg t.i.d. for 7 days for suspected pneumonia (with clavulanate if the patient is older than 65 years), and amoxicillin/clavulanate 875 mg/125 mg t.i.d. for 7 days for suspected acute exacerbations of COPD (Table 1). Nonetheless, this guideline is designed to serve as a reference for making informed and improved choices in prescribing. The decision to prescribe an antibiotic is solely at the discretion of the participating doctor. The trial is pragmatic, thus mirroring the real-life practices of doctors in Spain. Doctors may also prescribe antibiotics for longer regimens, such as 10-day durations, as shown in recent studies [36]. The decision to prescribe an antibiotic will always be made before randomizing the patient.

Patients in the intervention group will be treated accordingly, following the same recommendations as patients assigned to the control group, but they will be asked to return as soon as they feel better and are afebrile.

When deciding whether to discontinue the antibiotic course after a patient feels better during a consultation, the participating professionals must assess three key areas:

Overall improvement in the patient’s symptoms.Evaluate the vital signs, confirming that most of them are within the normal range and that the following clinical criteria are met: temperature <37 °C, blood pressure >90/60 mm Hg, pulse <100 beats/min, respiratory rate <20 breaths/min, and oxygen saturation >92%.Assess the CRP value and interpret the results according to the provided table based on current recommendations [37].

Patients who meet all these criteria will be asked to discontinue treatment. Otherwise, patients will be instructed to continue the course for 2 more days and, if they continue feeling better, to return for reassessment. In case of worsening symptoms, they will be advised to contact their doctor for clinical assessment. The doctor will then decide whether to recommend completing the full antibiotic course, changing the therapy, or making a referral.

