### Criteria for Discontinuing or Modifying Allocated Interventions

Due to the short intervention period after index consultation, the allocated intervention may only be discontinued for a given trial participant by the GP due to an unexpected event, hindering the GP from conducting or completing the allocated intervention, for example, acute worsening of the participant’s condition during index consultation, after consent has been given and allocation has been revealed. Moreover, the study may be discontinued for a given trial participant upon participant request or by withdrawal of informed consent. The data collected before the discontinuation or withdrawal of consent will be retained and used in the analyses; however, no further data will be obtained from the participant.

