### Statistical Methods

Statistical methods for primary and secondary outcomes: The characteristics of the study population will be described using frequencies for categorical variables and mean and SD for quantitative variables. To compare the clinical efficacy between the 2 strategies, we will analyze the difference in the proportion of recovered patients in each arm on day 14. Efficacy evaluation will be primarily based on intention-to-treat analysis in such a way that any event in any patient will be included in the group to which the patient was randomized, and per protocol analysis will be used as a secondary analysis. For all analyses, the level of significance will be *P*<.05.

Interim analyses: No interim analysis is planned.Methods for additional analyses (eg, subgroup analyses): We will conduct subgroup analyses of the primary outcome of participants with lower RTIs, and for acute rhinosinusitis.

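### Participants discontinued by the GP lose follow-up without withdrawing consent, which conflicts with the intention-to-treat population and risks outcome-related missing data

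*Protocol article*

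**What the plan says.** Five parts of the protocol article bear on this.

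- **Criteria for Discontinuing or Modifying Allocated Interventions.** The route for the GP is narrow: "the allocated intervention may only be discontinued for a given trial participant by the GP due to an unexpected event". The example is acute worsening during the index consultation, "after consent has been given and allocation has been revealed". The section then says that a participant may also leave the study on request or by withdrawing consent. It closes with one rule that names both discontinuation and withdrawn consent: what was recorded earlier is kept and analysed, but "no further data will be obtained from the participant".
- **Plans to Promote Participant Retention and Complete Follow-Up.** Outcome data from medical records are collected for all participants "except those who are discontinued by the GP or who have withdrawn informed consent before day 28".
- **Statistical Methods.** The primary analysis is by intention to treat, so that "any event in any patient will be included in the group to which the patient was randomized".
- **Methods in Analysis to Handle Protocol Nonadherence.** The primary analysis population is everyone, whatever their follow-up.
- **Assignment of Interventions: Blinding.** GPs and participants know the allocation.

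**The concern.** The retention section names GP discontinuation and withdrawal of consent as two separate reasons for not collecting record data. The first group has therefore not withdrawn consent. They agreed at enrolment to access to their medical records (Eligibility Criteria), so the article gives no consent-based reason to stop. Ending the allocated intervention is treated as if it were ending participation.

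An analysis cannot include an event that the protocol instructs staff not to collect. What would be lost includes reattendances and complications to day 28, such as emergency visits and hospital admissions. The day-14 primary outcome may be lost too, depending on how the discontinuation section is read.

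The decision belongs to someone who knows the arm, and the stated example is a clinical deterioration. Missing data of that kind can be informative. In a noninferiority comparison, losing failures from the intervention arm moves the result toward the claim being tested.

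**Working it through.** **Step 1. What each passage covers.**

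- The exception in the retention section concerns medical-record data only. The primary outcome comes from a day-14 phone call (Primary Efficacy Endpoint), so this exception alone does not remove it.
- The rule that ends data collection refers to discontinuation or withdrawal of consent. The more natural reading includes discontinuation by the GP, and then the calls stop too. A narrower reading, limited to participants who leave on request or withdraw consent, is possible.
- On either reading, GP-discontinued participants lose record-based outcomes. On the broader reading they lose the day 7, 14 and 28 calls as well.

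**Step 2. The plan's sample size.** Inputs from Sample Size: 85% resolution in control (taken as equal in both arms), margin 10 points, power 80%, 15% unevaluable.

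- n per arm = (1.960 + 0.842)² × 2 × 0.85 × 0.15 / 0.10² = 200.1, rounded up to 201, or 402 in total.
- 201 / 0.85 = 236.5, rounded up to 237, or 474 in total.

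Both stated totals reproduce, with a one-sided 2.5% level. A one-sided 5% level gives 158 per arm and does not. The one-sided 2.5% level is used below.

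**Step 3. Type I error if losses fall in one arm only.** The article gives no rate of GP discontinuation, so the share f is an assumption. Worst case: a share f of the intervention arm is discontinued, all are failures and are left out, and none are lost in control. The true rates are 75% and 85%, exactly at the margin.

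- Observed intervention rate: p = 0.75 / (1 − f)
- SE = √[p(1 − p) / (n(1 − f)) + 0.85 × 0.15 / n]
- P(noninferiority declared) = 1 − Φ(1.96 − (p − 0.85 + 0.10) / SE)

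For f = 2% and n = 201: p = 0.7653 and SE = 0.0393. Then (0.7653 − 0.75) / 0.0393 = 0.39, and 1 − Φ(1.57) = 0.058.

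| f (assumed) | observed p | n = 201 per arm | n = 237 per arm |
|---|---|---|---|
| 0 | 0.7500 | 0.025 | 0.025 |
| 1% | 0.7576 | 0.039 | 0.040 |
| 2% | 0.7653 | 0.058 | 0.062 |
| 3% | 0.7732 | 0.086 | 0.094 |
| 5% | 0.7895 | 0.173 | 0.196 |

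**Step 4. Equal loss in both arms.** With 237 per arm and the same share of failures left out of each, the observed difference is −0.10 / (1 − f). That is −10.2 points at 2% and −10.5 points at 5%. The error is 0.022 and 0.017, so there is no inflation.

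**Step 5. Counted instead of left out.** If these participants stay in the denominator as failures, p remains 0.75 and the error remains 0.025.

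**Step 6. A borderline result.** Take 237 per arm, control at 85% and intervention at 81.5% (expected counts, not whole patients).

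- Everyone counted: −3.5 − 1.96 × 3.43 = −10.2 points; noninferiority is not shown.
- Two intervention failures left out: rate 82.2%, lower limit −9.5 points; noninferiority is shown.
- Five left out: lower limit −8.4 points.

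**The case against.** The case against a serious problem is strong in several respects.

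- **The route is narrow.** Only an unexpected event qualifies, and the one example is at the index consultation. The antibiotic is chosen before randomization and both arms start on the same recommendations, so worsening at that visit is not a failure of early stopping. An arm difference would have to come from GPs acting on knowledge of the allocation. This stands, and it makes the group probably small.
- **Later worsening stays in follow-up.** For intervention patients who worsen after reassessment, Interventions says: "The doctor will then decide whether to recommend completing the full antibiotic course, changing the therapy, or making a referral". That is a treatment decision. The day 7 and 14 calls record complications, reattendance and treatment changes. A reader might infer that early failures disappear from the trial; these passages do not support that.
- **Intention to treat remains possible.** A reader might infer that the analysis cannot be done at all. But these participants stay in the randomized population, earlier data are kept, and an analysis plan, which is not shown, could count or impute a missing day-14 outcome.
- **The discontinuation rule is ambiguous.** This also stands, and it is why the effect on the primary endpoint is stated conditionally.

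What these points do not answer is that the record exception is a stated data-collection rule. An analysis plan can assign a value to a missing day-14 outcome. It cannot recover complications or reattendances that were never collected. Ending collection when consent is withdrawn is proper and is not criticized.

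**Conclusion.** The point holds as an internal conflict. The record exception, and on its more natural reading the discontinuation rule, ends outcome collection for participants who still consent, while the statistical sections promise that all participants and all their events count. The loss is decided by an unblinded GP and its stated example is clinical worsening, so it can be related to outcome.

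The number affected is probably small and the bias cannot be sized from the article. The rise from 2.5% to about 6% rests on three assumptions that the article does not supply: a 2% rate, every lost participant a failure, and no loss in control. It also requires that they be left out of the analysis. It is a worst case, not a forecast. With equal loss, or if those lost are counted as failures, there is no inflation. Step 6 shows only that a handful of one-sided exclusions could change a borderline result.

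**What to change.** - In the discontinuation section, separate stopping the allocated intervention from withdrawing consent. State that the first does not end follow-up and that data collection stops only on the second.
- In the retention section, remove GP-discontinued participants from the exception.
- State that they keep the day 7, 14 and 28 calls and the record review, and are analysed in their randomized arm.
- Report GP discontinuations by arm with reasons, so that readers can see whether they are balanced.

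The cost is a few sentences of protocol text, ideally before recruitment starts in October 2025, otherwise by prompt amendment. The calls and record review are already planned for participants in both arms, no visit is added, and the sample size of 474 is unchanged.

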### Statistical Methods

Statistical methods for primary and secondary outcomes: The characteristics of the study population will be described using frequencies for categorical variables and mean and SD for quantitative variables. To compare the clinical efficacy between the 2 strategies, we will analyze the difference in the proportion of recovered patients in each arm on day 14. Efficacy evaluation will be primarily based on intention-to-treat analysis in such a way that any event in any patient will be included in the group to which the patient was randomized, and per protocol analysis will be used as a secondary analysis. For all analyses, the level of significance will be *P*<.05.

Interim analyses: No interim analysis is planned.Methods for additional analyses (eg, subgroup analyses): We will conduct subgroup analyses of the primary outcome of participants with lower RTIs, and for acute rhinosinusitis.

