A promising strategy to reduce unnecessary antibiotic exposure involves tailoring treatment duration based on individual response. Conventional stewardship programs often fail to address overtreatment in patients who genuinely need antibiotics. Encouraging shorter, evidence-based durations may be a more practical and acceptable alternative, as shown in qualitative research [25]. The optimal antibiotic duration likely varies by individual. Factors such as age, comorbidities, immune status, bacterial load, and organ function influence how patients metabolize and respond to treatment [26,27]. A one-size-fits-all approach risks under- or overtreatment. For instance, in a landmark study, 3-day treatment was as effective as 8 days in 78.5% of patients hospitalized with mild to moderate pneumonia who had improved by day 3 [7]. It would not be unreasonable to think that the percentage of patients with pneumonia who feel better after 3 days of therapy would be even higher in primary care.

When a nonbacterial or self-limiting infection is suspected, the priority should be to avoid initiating antibiotics. For patients already on fixed-duration antibiotic courses, clinicians should consider advising discontinuation once symptoms are resolved, unless the infection is deemed potentially serious [25]. In such cases, reassessment with clinical examination or point-of-care tools like C-reactive protein (CRP) testing may be warranted before stopping treatment. Interestingly, one-third of patients already stop antibiotics on their own once they feel better. Studies using electronic monitoring show poor adherence to prescribed durations in real-world settings [28]. This emphasizes the need to align prescribing practices with patient behavior and current evidence.

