Day 0 (inclusion date at the center): Patients meeting the inclusion criteria will be invited to join the study by their GP. After obtaining informed consent, patients will be randomized into either the control group (receiving a full course of β-lactam therapy for at least 7 days) or the intervention group (instructed to return for assessment upon feeling better and being afebrile). The GPs will complete a case report form on day 0 (inclusion day), recording details such as age, inclusion and exclusion criteria, symptoms, date of symptom onset, comorbidities, concomitant medication, quality-of-life questionnaire (EQ-5D-5L instrument), randomization, assigned group, and details of the antibiotic administered. Patients will also be provided with a symptom diary (web-based or paper-based)From day 1 until the last day of the antibiotic regimen duration (at the center, only for patients assigned to the intervention group): For patients assigned to the intervention, they will be asked to return to the center for clinical reassessment and CRP rapid testing by the professional. Each center will organize ways to make it easy for patients to reach out and schedule an appointment as soon as they feel better (eg, phone number and web-based page). To decide whether to discontinue the antibiotic course when the patient reports feeling better during the consultation, three types of assessment are needed: (1) overall improvement in the patient’s symptoms; (2) signal signs are in normal range (temperature <37 °C; blood pressure >90/60 mm Hg; pulse < 100 beats/minute; respiratory rate <20 breaths/minute, and oxygen saturation >92%), and (3) CRP value is lower than the prespecified values depending on the day of the visit. All this information will be recorded in the electronic case report form (e-CRF; Table 1)Day 3±1 (phone call, only for patients assigned to the intervention group): A reminder phone call for all patients assigned to the intervention group will be made on this day. They will be asked how they feel and reminded to reach out to the center as soon as they feel better for a discontinuation assessmentDay 7 (phone call): An early clinical efficacy outcome will be assessed during this call, including the clinical progression of signs and symptoms, treatment adherence, adverse reactions, any complications, reattendance visits, changes to the assigned treatment or concomitant medication, and the use of antibiotics other than the study drugDay 14 (phone call): The main clinical efficacy outcome and some secondary outcomes, including clinical progression of signs and symptoms, compliance with the study treatment, EQ-5D-5L instrument, adverse reactions, any complications, reattendance visits, changes in the assigned treatment or concomitant medication, including the use of antibiotics other than the study medication, will be assessed. Patients will be asked to return their diariesDay 28 (phone call): Patients will be contacted for information on the number of reconsultations, complications, and the quality-of-life (EQ-5D-5L) instrument

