
#### Sample Size

We assumed 85% clinical recovery in the group assigned to the full antibiotic course based on some studies [12,42-44]. Considering a power of 80%, a level of significance of 5%, one-sided noninferiority margin of 10%, as recommended by the guideline on the evaluation of medicinal products indicated for treatment of bacterial infections issued by the European Medicines Agency in 2022 [45], which gave a sample size of 402 patients. Assuming that the primary outcome could not be evaluated in 15% of patients, 474 patients needed to be included in the study (237 in the control group and 237 in the intervention group).

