#### Assignment of Interventions: Allocation

##### Sequence Generation

Patients fulfilling the inclusion criteria will be asked to participate in the trial. All patients who agree to participate and provide signed informed consent will receive an increasing sequential patient number and be randomly assigned to one of the 2 treatment groups in a 1:1 ratio stratified per main diagnosis, one for acute rhinosinusitis and another one for lower RTI.

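### The primary risk difference is stated without any adjustment, so the diagnosis stratum and the day-0 baseline data go unused: a modest, cheap efficiency gain to prespecify, not an error

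*Protocol article*

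**What the plan says.** - **Primary comparison (Statistical Methods):** "we will analyze the difference in the proportion of recovered patients in each arm on day 14". The section names no model, covariate set or interval method. It uses neither the word adjusted nor unadjusted.
- **Sample size (Sample Size):** "We assumed 85% clinical recovery in the group assigned to the full antibiotic course", with 80% power, a 5% significance level and a 10-point margin, "which gave a sample size of 402 patients". Then: "Assuming that the primary outcome could not be evaluated in 15% of patients, 474 patients needed to be included in the study".
- **Randomization (Sequence Generation):** "in a 1:1 ratio stratified per main diagnosis, one for acute rhinosinusitis and another one for lower RTI". In the analysis, diagnosis appears only as the basis for subgroup analyses of the primary outcome.
- **Baseline data (Participant Timeline, day 0):** the case report form is completed at inclusion, "recording details such as age, inclusion and exclusion criteria, symptoms, date of symptom onset, comorbidities", together with concomitant medication and the EQ-5D-5L.
- **Relevance of those data (Introduction):** "Factors such as age, comorbidities, immune status, bacterial load, and organ function influence how patients metabolize and respond to treatment". This is a qualitative statement made in support of individualized duration. No odds ratio, explained variance or subgroup rate is given.

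**The concern.** The Sample Size and Statistical Methods sections, read together, point most naturally to an unadjusted difference in proportions. Yet the protocol itself treats some baseline factors as important. Table 1 varies the antibiotic by age over 65 and by COPD. Table 2 makes the stopping decision depend on COPD, comorbidity and advanced age. The lower RTI stratum also pools pneumonia, acute bronchitis and COPD exacerbations across ages 18 to 75, so much of any prognostic variation would lie inside a stratum, where stratified randomization does not reach it.

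At stake is precision. If these variables predict day-14 resolution, an adjusted estimate of the same risk difference has a smaller standard error and a better chance of showing noninferiority when it is true.

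Timing matters as well. The Blinding section says that outcome assessors and data analysts are hard to blind. Covariates chosen after data have been seen, in an open-label noninferiority trial, would carry little credibility. The gain is available only if the set is fixed beforehand.

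**Working it through.** **Inputs from the article.** Control resolution 85%; margin 10 points; power 80%; significance level 5%; 402 evaluable; 15% not evaluable; 474 total. Equal resolution in both arms is not stated but is implied, because it reproduces the 402.

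**Assumed input.** R², the share of outcome variance explained by the baseline variables. The article gives no figure, so the range 0 to 0.15 is shown.

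**Step 1: reproduce the plan's figure.** With unpooled variance,

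n per arm = 2 × 0.85 × 0.15 × (z₁₋α + z₀.₈)² / 0.10².

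- One-sided 2.5%: 0.255 × (1.960 + 0.842)² / 0.01 ≈ 200.2, rounded up to 201 per arm, 402 in total. Dividing by 0.85: 201 / 0.85 = 236.5, rounded up to 237 per arm, 474 in total. Both stated figures reproduce.
- One-sided 5%: 158 per arm, 316 in total. This does not reproduce.

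The plan's figure is therefore an unadjusted calculation at one-sided 2.5%.

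**Step 2: unadjusted power.** SE = √(2 × 0.1275 / 201) = 0.0356. Power = Φ(0.10 / 0.0356 − 1.960) = 80.2%.

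**Step 3: adjusted power.** Multiply the variance by (1 − R²), keeping the margin and alpha. The equivalent number of extra patients is 402 / (1 − R²) − 402.

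| Assumed R² | SE | 95% half-width (points) | Power | Equivalent extra evaluable patients |
|---|---|---|---|---|
| 0 | 0.0356 | 6.98 | 80.2% | 0 |
| 0.01 | 0.0354 | 6.95 | 80.6% | 4 |
| 0.05 | 0.0347 | 6.80 | 82.1% | 21 |
| 0.10 | 0.0338 | 6.62 | 84.1% | 45 |
| 0.15 | 0.0328 | 6.44 | 86.1% | 71 |

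**Step 4: the stratum alone.** For two equal strata, R² = 0.25 × (p₁ − p₂)² / 0.1275. Assumed rates of 80% and 90% give 0.02, which is 81.0% power, a gain of under one point. Rates of 83% and 87% give 0.003. Most of any benefit must come from the other covariates.

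**Step 5: simulation check.** Settings: 3,000 trials each, 201 per arm, a logistic model with four covariates, standardized to the marginal risk difference with an influence-function standard error. At 80% power the Monte Carlo error of one rate is √(0.8 × 0.2 / 3000) ≈ 0.7 points.

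| R² | Unadjusted power | Adjusted power |
|---|---|---|
| 0 | 79.7% | 79.5% |
| 0.02 | 80.3% | 80.7% |
| 0.061 | 80.9% | 82.3% |
| 0.117 | 79.9% | 84.7% |

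A second set of runs looked at the error rate when the true difference equals the margin. The false noninferiority rate was 2.5% adjusted against 2.6% unadjusted at R² 0.045, and 2.8% against 2.6% at R² 0.096. The Monte Carlo error there is about 0.3 points, so no inflation is visible.

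**The case against.** The strongest case against is that nothing here is wrong. The stated comparison names an effect measure, and a standardized risk difference is also a difference in proportions recovered. The article condenses a fuller protocol that is not shown, and covariates and models are commonly left to that document or to the analysis plan. An unadjusted difference is valid under randomization and matches the sample size exactly. All of this stands, and it limits the point to an improvement that is conditional on adjustment not already being specified elsewhere.

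A reader might infer four stronger things that the documents do not support.

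- **That the protocol commits to an unadjusted analysis.** This is the natural reading, but the words are not there.
- **That a material amount of power is being lost.** This needs a prognostic strength the article never gives. Eligibility also narrows the prognostic range: pneumonia with CRB-65 of 1 or more, very severe COPD, immunocompromise and active neoplasia are all excluded.
- **That the trial has no slack.** The 80% applies to 402 evaluable patients. If all 474 contributed an outcome at 85% resolution, unadjusted power would be Φ(0.10 / 0.0328 − 1.960) = 86.2%, about what adjustment yields at 402 only when R² is 0.15.
- **That chance imbalance in age or comorbidity, or the small number of patients per center, threatens the result.** Randomization is not stratified by center, and the unadjusted interval already covers chance imbalance. It does not bias the test.

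One practical objection also stands. Days since onset means different things in the two diagnoses: a cough may have lasted up to 21 days, while rhinosinusitis can qualify through lack of improvement within 10 days.

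**Conclusion.** The point holds as a modest efficiency improvement. The stated primary analysis is valid and the trial is adequately sized for it. It makes no use of the stratification factor or of the baseline data collected at day 0. Using them would leave the estimand and the 10-point margin unchanged.

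The gain at 201 evaluable patients per arm is between nothing and about 6 power points, from 80.2% to at most 86.1%, over assumed R² values of 0 to 0.15. At R² of 0.01 to 0.05 it is about 0.4 to 2 points. With covariates that are not prognostic, the gain is nil or the loss trivial. These figures rest on 85% resolution in both arms, one-sided 2.5%, and an R² that is an assumption throughout.

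**What to change.** Unless it is already prespecified elsewhere, add to Statistical Methods that the primary estimate is the day-14 risk difference standardized over the diagnosis stratum and a short, named set of day-0 variables. Examples are age, COPD or other relevant comorbidity, and days since symptom onset. If days since onset is used, let its effect differ by diagnosis.

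A logistic model with marginal standardization and a robust or influence-function standard error is sufficient. Compare the confidence limit with the same 10-point margin, and report the unadjusted difference as a sensitivity analysis. Leave the sample size as it is.

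CRP cannot be one of the covariates: Table 3 schedules it only at the intervention-arm reassessment visit, after randomization.

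The cost is one sentence and a few lines of code, with no new data collection. The one constraint is that the covariates and their coding must be fixed in advance, before anyone analyzing the trial sees outcomes by arm.
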